### Study participants and recruitment

We will recruit 280 patients scheduled to undergo laparoscopic resection of gastric and colorectal tumors. These patients will be recruited from Beijing Friendship Hospital affiliated with Capital Medical University after they meet the eligibility criteria and sign their informed consent. We plan to enroll the first patient on July 1, 2019 and to end on December 31, 2020. All participants will sign the informed consent form for participating in the clinical trial and the informed consent form for collecting blood samples.

#### Inclusion criteria

Inclusion criteria are as follows: (1) aged 18–70 years, regardless of gender; (2) undergoing endotracheal intubation and laparoscopic abdominal tumor resection under general anesthesia (stomach, colon, and rectum); (3) body mass index (BMI) 18–30 kg/m^2^ (BMI = weight in kilograms / height in meters squared); (4) American Society of Anesthesiologists (ASA) classification levels I–III; (5) requirement for a postoperative analgesia pump and signing of informed consent; and (6) volunteering to participate in this study and sign the informed consent.

#### Exclusion criteria

Exclusion criteria are as follows: (1) surgical incision or scar on the meridian of L14 / PC6 / ST36 / ST37; (2) local skin infection at acupoints; (3) upper limb or lower limb nerve injury; (4) a history of spinal surgery; (5) participation in other clinical trials within the past 4 weeks; (6) inability to understand the visual analog scale (VAS) score and numeric rating scale (NRS) score or to use patient-controlled analgesia (PCA); (7) presence of a pacemaker; (8) preoperative complications involving severe CNS diseases or severe mental diseases; (9) operations requiring enterostomy or conversion to open surgery; or (10) necessity of transfer to the intensive care unit (ICU) for treatment after surgery.

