### Randomization and blinding

This is a single-blinded study. The doctors from the traditional Chinese department who will conduct the TEAS stimulation and the anesthesiologists will know the grouping information and participants. The observers of major outcomes after surgery will be blinded. Randomization will be conducted by a computer-generated blocked randomization list with 70 blocks of four patients per block. The participants will be consecutively randomly assigned to the TEAS group or the sham group at a ratio of 1:1. Allocation shall proceed via duplicate, sealed, numbered envelopes, which will be stored by the clinical trial quality control inspectors and the main person in charge of this research group. The blind bottom shall not be opened without reason during the trial. The outcome assessors and the statisticians will not participate in the treatment, they will perform the outcome evaluation and the statistical analysis independently.

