### Interventions

Patients receiving TEAS treatment will be treated bilaterally at four acupoints: Hegu (L14) and Neiguan (PC6), as well as Zusanli (ST36) and Shangjuxu (ST37). L14 is an acupoint of the hand yangming large intestine meridian. It is located on the dorsum of the hand between the first and second metacarpal bones (Fig. 2). PC6 belongs to the pericardium meridian. It is located between the flexor carpi radialis muscle tendon and the palmaris longus tendon, 2 cun above the rasceta (Fig. 2). ST36 and ST37 are acupoints of the foot yangming stomach meridian. ST36 is located on the lateral side of the lower leg, 3 cun below Dubi and one finger width lateral to the anterior border of the tibia (Fig. 3). ST37 is located 3 cuns below ST36. An electrode with wire will be attached to the site of these acupoints. The wire is connected to the HANS acupoint nerve stimulator (HANS-200A, Nanjing Jisheng Medical Technology Co., Ltd., China). TEAS stimulation uses a dense-dispersed wave with frequencies of 2 and 100 Hz alternating every 3 s. The waveform is a symmetric biphasic curve. The stimulation intensity will be set to the level of maximum tolerance for each patient. During the operation, the TEAS stimulation will span from before the induction to the end of the operation. On the first, second, and third days after surgery, the acupuncture doctor will arrive at the ward in the morning at 09:00 to administer TEAS stimulation at the same acupoints for 30 min. This stimulation will be continued until the patients’ flatus recovery.

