### Outcome assessment

A blind observer from the Data Monitoring Committee (DMC) will collect all outcome data after surgery. The primary outcome of this study will be time to the first bowel motion by auscultation. The same surgical residents will listen to the bowel sounds every 4 h postoperatively. Time to first bowel motion is the duration until regular bowel sounds (more than two sounds every minute) are first heard after surgery [14].

The secondary endpoints will include the time to first flatus and time to defecation. This information will be obtained from participant questionnaires filled out once daily with the help of nurse staff. To observe changes in plasma brain–gut peptides, such as 5-HT, SP, VIP, gastrin, and CCK, we will collect venous blood from patients before the operation and on the first and third days after the operation. We will then centrifuge and freeze the plasma supernatant for later testing. We cooperate with our clinical experimental center to collect, code, centrifuge, freeze store, store, and test blood samples by a professional team. Secondary endpoints will also include VAS score of postoperative pain, vomiting and nausea, length of stay in the ICU, length and cost of stay in the hospital, as well as clinical complications such as fever, pneumonia, wound infection, and bleeding. Secondary outcome will be assessed by the medical team. The length of hospital stay is calculated as the number of days from the date of the operation to the date of discharge. Criteria for hospital discharge will include stable vital signs, the ability to tolerate solid foods after defecation without nausea or vomiting, and the occurrence of no other complications after the operation.

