### Statistical methods

Statisticians are responsible for negotiating with major researchers to develop statistical analysis plans, establish databases, and conduct statistics with the SPSS statistical analysis system. All data will be collated by statisticians. The intention processing principle in SPSS 22.0 will be used for the data analysis. A unilateral test will be used for statistical results, and a *P* value < 0.05 will be considered statistically significant. The results will be expressed as the mean ± standard deviation. The t-test will be used for the normality and homogeneity of data, the hypothesis test of superiority will be used for major outcome indicators, the chi-square test will be used for normal distribution data, and the rank sum test or Fisher’s exact probability method will be used for non-normal distribution data. Statistical methods for the main efficacy indicators have been determined by the Capital Medical University statistical department.

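### Exclusion criteria 9 and 10 reach events that occur after allocation, so as written they remove randomised patients and leave the ICU-stay endpoint with no non-zero values

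*Protocol article*

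**What the plan says.** All references are to the protocol article.

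- **Exclusion criteria.** Two items concern the operation and its aftermath: "9) operations requiring enterostomy or conversion to open surgery; or (10) necessity of transfer to the intensive care unit (ICU) for treatment after surgery".
- **Interventions.** "During the operation, the TEAS stimulation will span from before the induction to the end of the operation". The sham group has its electrodes at different sites, without current.
- **Randomization and blinding.** "The doctors from the traditional Chinese department who will conduct the TEAS stimulation and the anesthesiologists will know the grouping information and participants". Observers of the main outcomes are blinded. The time of randomisation is not stated.
- **Outcome assessment.** The primary outcome is time to regular bowel sounds, checked every 4 h. The secondary endpoints include "length of stay in the ICU".
- **Statistical methods.** "The intention processing principle in SPSS 22.0 will be used for the data analysis". This is apparently intention-to-treat.
- **Data collection methods and monitoring.** Names a whole analysis set and a program set (apparently per-protocol), without saying where a patient who meets criterion 9 or 10 after allocation belongs.
- **Discharge criteria.** Protocol violation and serious adverse events are separate grounds for a participant to leave the trial.

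**The concern.** An exclusion criterion should be decidable before randomisation. One that is triggered during or after the operation, once the allocated treatment is running, selects patients on what happened to them in the trial. The groups compared are then no longer the randomised groups.

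The loss is unlikely to be neutral for this outcome. Patients who are converted, receive an unplanned stoma or go to the ICU plausibly regain bowel sounds later, and the primary outcome is the time to those sounds. If TEAS affects who is removed, or if knowledge of the allocation does, the comparison is biased. Equal numbers removed per arm would not show otherwise, because different kinds of patients may have gone from each.

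There is also a plain internal conflict: a trial that excludes everyone who needs the ICU after surgery cannot compare length of ICU stay.

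**Working it through.** **Step 1. Order of events.**

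| Event | When it is known | Relative to allocation |
|---|---|---|
| Allocation | Before induction (inferred: stimulation starts then, and electrode sites differ by arm) | – |
| Conversion to open surgery | During the operation | Always after |
| Enterostomy | At planning, or during the operation | Before or after |
| ICU transfer after surgery | Foreseen beforehand, or after the operation | Before or after |

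Entry is already limited to patients scheduled for laparoscopic resection. The conversion clause can therefore act only on patients who have been allocated and are under treatment.

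**Step 2. Criterion 10 against the endpoint.** If every patient needing ICU transfer after surgery is excluded, each remaining patient has an ICU stay of 0 days in both arms, and nothing is left to compare.

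**Step 3. The plan's own sample size.** Inputs from Sample size calculation: hazard ratio 1.5, 1:1 allocation, power 0.90, one-sided alpha 0.05, 256 effective cases, 10% loss, 280 in total.

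Schoenfeld events: D = 4(z_alpha + z_power)² / (ln 1.5)², with ln 1.5 = 0.4055.

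- Two-sided 0.05: 4(1.960 + 1.282)² / 0.1644 = 256. This matches the stated figure.
- One-sided 0.05, as stated: 4(1.645 + 1.282)² / 0.1644 = 209. This does not match.

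That mismatch is a separate matter; because of it, power is shown both ways below. The planned loss leaves 280 × 0.9 = 252 patients.

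**Step 4. Effect of the removals on power.** The document gives no rate for criteria 9 and 10, so x is an assumption. It is also assumed that the removals come on top of the 10% loss and that every remaining patient has the event.

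n = 280 × (1 − x) × 0.9; power = Φ(√(n/4) × ln 1.5 − z_alpha).

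| Removed, x | n | Power, two-sided 0.05 | Power, one-sided 0.05 |
|---|---|---|---|
| 0% | 252 | 0.896 | 0.942 |
| 5% | 239 | 0.880 | 0.932 |
| 10% | 227 | 0.863 | 0.920 |
| 15% | 214 | 0.843 | 0.907 |
| 20% | 202 | 0.821 | 0.891 |

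Against the like-for-like baseline of 252, the two-sided drop is 1.6, 3.3 and 5.3 percentage points at 5%, 10% and 15%. If the 10% allowance already covers these removals, there is no further drop. The bias cannot be sized, because the document gives neither the removal rates by arm nor the recovery times of these patients.

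**The case against.** **The criteria may be meant for screening.** Patients are recruited after meeting the eligibility criteria, and a planned stoma or a foreseen ICU need can be known then. A reader might infer that all three events necessarily follow randomisation; the document does not support that, and only conversion always does. But neither criterion is limited to what is planned, and conversion has no screening reading in a trial of scheduled laparoscopic surgery.

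**Removal from the analysis is not spelled out.** These patients might stay in the whole analysis set, and a statistical analysis plan not shown may say so. A reader should therefore not call this a proven departure from intention-to-treat, or call the ICU endpoint empty beyond doubt. Still, the stated rule makes such patients ineligible and nothing says that they are kept. The text needs reconciling whatever another document adds.

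**The events are not all outcomes.** A reader might say that patients are removed on their outcomes. Conversion and enterostomy are not listed endpoints, so post-randomisation events is the exact description.

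**The route to bias is partly conjecture.** The anesthesiologists know the allocation, but the document does not say who decides on ICU transfer, and surgeons are not named among those who know. Differential removal is a risk, not an established fact. Slower recovery in these patients is plausible but has no figure behind it here.

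**The trial is not shown to be underpowered.** A reader might set the reduced numbers against all 280 patients observed (two-sided power 0.924). That would charge the planned 10% loss to these criteria. At the stated one-sided level, power stays above 0.90 for assumed removals up to 15%.

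**Conclusion.** The point holds. As written, criterion 9 (always for conversion, sometimes for enterostomy) and criterion 10 (for any unforeseen ICU transfer) remove patients after allocation and after treatment has begun. This conflicts with the intention principle under Statistical methods, and criterion 10 conflicts with the ICU-stay endpoint.

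The conclusion rests on one inference, that allocation precedes induction; the description of the intervention leaves no other reading. The harm is possible selection bias in the primary comparison, of unknown size and direction. The effect on power is secondary: under assumed removals of 5% to 15% on top of the planned loss, two-sided power is about 0.88 to 0.84 instead of 0.896. It should be settled before analysis. The article reports 106 participants recruited and the trial ongoing, so there is still time.

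**What to change.** 1. Limit criteria 9 and 10 to what is planned or known before randomisation: planned enterostomy, planned open surgery, planned ICU admission.
2. Keep every randomised patient in follow-up and in the primary analysis, including those with unplanned conversion, stoma or ICU transfer.
3. Make the analysis-set wording under Data collection methods and monitoring, and the Discharge criteria, consistent with this. Otherwise a patient kept under the new criterion 10 could still be lost as a protocol violation or serious adverse event. This concerns follow-up and analysis only; when treatment stops is a clinical matter outside this point.
4. Score ICU stay as 0 days for patients not admitted.
5. Report results without patients who had an unplanned conversion, stoma or ICU transfer as a sensitivity analysis only.
6. For patients already removed under criteria 9 or 10, include them where outcome records exist. Otherwise censor them at the last bowel-sound assessment, and report their number by arm. Such censoring treats the removal as unrelated to recovery time, which is doubtful here, so the counts by arm matter.

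Cost: an amendment to the wording, a slight dilution of the effect from slow-recovering patients, and some incomplete outcome data. The primary outcome depends on 4-hourly auscultation, which may not have been recorded for patients already removed and may be harder to obtain in the ICU.

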#### Discharge criteria

Discharge criteria are as follows: (1) requirement for individuals to withdraw during the test; (2) violation of the test program; and (3) occurrence of serious adverse events (AEs).

### Interventions

Patients receiving TEAS treatment will be treated bilaterally at four acupoints: Hegu (L14) and Neiguan (PC6), as well as Zusanli (ST36) and Shangjuxu (ST37). L14 is an acupoint of the hand yangming large intestine meridian. It is located on the dorsum of the hand between the first and second metacarpal bones (Fig. 2). PC6 belongs to the pericardium meridian. It is located between the flexor carpi radialis muscle tendon and the palmaris longus tendon, 2 cun above the rasceta (Fig. 2). ST36 and ST37 are acupoints of the foot yangming stomach meridian. ST36 is located on the lateral side of the lower leg, 3 cun below Dubi and one finger width lateral to the anterior border of the tibia (Fig. 3). ST37 is located 3 cuns below ST36. An electrode with wire will be attached to the site of these acupoints. The wire is connected to the HANS acupoint nerve stimulator (HANS-200A, Nanjing Jisheng Medical Technology Co., Ltd., China). TEAS stimulation uses a dense-dispersed wave with frequencies of 2 and 100 Hz alternating every 3 s. The waveform is a symmetric biphasic curve. The stimulation intensity will be set to the level of maximum tolerance for each patient. During the operation, the TEAS stimulation will span from before the induction to the end of the operation. On the first, second, and third days after surgery, the acupuncture doctor will arrive at the ward in the morning at 09:00 to administer TEAS stimulation at the same acupoints for 30 min. This stimulation will be continued until the patients’ flatus recovery.

**Fig. 2 Fig2:**
[figure not shown]
The location of L14, PC6. L14 is the Hegu acupoint; PC6 is the Neiguan acupoint

**Fig. 3 Fig3:**
[figure not shown]
The location of ST36, ST37. ST36 is the Zusanli acupoint; ST37 is the Shangjvxu acupoint

In the sham group, the sham points are at 7 cun and 9 cun above Shenmen (HT7) and outside 1 cun (Fig. 4). The other two sham points are at 9 cun and 12 cun above the Kunlun (BL60) (Fig. 5). There are no meridian and channels through these four sites; thus, we will use these positions as our sham points. We will put the electrode on the sham points and connect it to the HANS stimulator but not administer any stimulation. The same doctor will go to the ward, put the electrode on these points, and connect it to the stimulator (not open) at the same time after surgery, until the first flatus recovery.

**Fig. 4 Fig4:**
[figure not shown]
The location of sham points 1 and 2. HT7 is the Shenmen acupoint. Cun is the unit of length

**Fig. 5 Fig5:**
[figure not shown]
The location of sham points 3 and 4. BL60 is the Kunlun acupoint. Cun is the unit of length

The anesthesia is total intravenous anesthesia; no epidural, paravertebral block, TAP, or other nerve block is added during the operation. Before the end of the operation, 0.5% ropivacaine incision infiltration block will be performed in the incision of endoscope. The general anesthesia drugs and methods during the operation are determined by the chief anesthesiologist and conform to the treatment routine and work habits.

### Postoperative analgesia measures and remedial plan

The analgesic pump configuration: after the operation, the intravenous analgesic pump was connected and the analgesic formula sufentanil 250 μg was added with normal saline to 250 mL, 2 mL/h, and PCA 3 mL at an interval of 15 min. (1) Analgesia recovery: participants were given Flubiprofen 50 mg/intravenous glucose tolerance test in the ward when the pain VAS score was ≥ 4 points and the pain score was still ≥ 4 points after five consecutive effective PCA compressions. (2) Remedy of nausea and vomiting: the NRS method was used for nausea score. When the nausea score was ≥ 7 points or vomiting ≥ 1 time, serotonin 3 receptor antagonist was given. The remedial medication should be recorded in the remedial medication list. (3) Concomitant medication record: concomitant medication during the trial period (from the start of surgery to 5 days after the end of surgery).

### Outcome assessment

A blind observer from the Data Monitoring Committee (DMC) will collect all outcome data after surgery. The primary outcome of this study will be time to the first bowel motion by auscultation. The same surgical residents will listen to the bowel sounds every 4 h postoperatively. Time to first bowel motion is the duration until regular bowel sounds (more than two sounds every minute) are first heard after surgery [14].

The secondary endpoints will include the time to first flatus and time to defecation. This information will be obtained from participant questionnaires filled out once daily with the help of nurse staff. To observe changes in plasma brain–gut peptides, such as 5-HT, SP, VIP, gastrin, and CCK, we will collect venous blood from patients before the operation and on the first and third days after the operation. We will then centrifuge and freeze the plasma supernatant for later testing. We cooperate with our clinical experimental center to collect, code, centrifuge, freeze store, store, and test blood samples by a professional team. Secondary endpoints will also include VAS score of postoperative pain, vomiting and nausea, length of stay in the ICU, length and cost of stay in the hospital, as well as clinical complications such as fever, pneumonia, wound infection, and bleeding. Secondary outcome will be assessed by the medical team. The length of hospital stay is calculated as the number of days from the date of the operation to the date of discharge. Criteria for hospital discharge will include stable vital signs, the ability to tolerate solid foods after defecation without nausea or vomiting, and the occurrence of no other complications after the operation.

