Recently, the brain–gut axis, serving as a bridge between the central nervous system (CNS) and the GI tract [8, 9], has been proved to be one of the possible mechanisms of acupuncture improving GI. Through the brain–gut axis, signals from the brain affect the sensory, motor, and endocrine modalities, as well as the microflora of the GI gut. Similarly, visceral information from the microbiota may also influence brain functions [8]. In our previous studies, our research group also found that electroacupuncture stimulation of Zusanli (ST36) could lead to imaging changes in different brain regions observed by functional magnetic resonance imaging (fMRI) [10]. These results demonstrated that acupuncture may act through the brain–gut axis. Brain–gut peptides are distributed along the GI tract and in the CNS and are involved in the modulation of GI tract processing [11]. The secretion of substance P (SP) and vasoactive intestinal polypeptide (VIP) are decreased, motilin and cholecystokinin (CCK) are increased after treatment with electrical acupuncture (EA) in rats with irritable bowel syndrome (IBS) [12, 13]. However, until now, most research on this mechanism has focused on animal studies and the treatment effect of acupuncture or transcutaneous electrical acupuncture stimulation (TEAS) on patients after abdominal surgery—whether the prevention effect of TEAS on PGD through brain–gut peptides or not—is still unclear.

Based on previous studies, our aim is to confirm the preventive effect of TEAS on PGD in patients undergoing abdominal surgery. Changes in the perioperative brain–gut peptides may prove that the regulation of GI function by TEAS stimulation plays a role through the brain–intestinal axis. Health economic indicators (length of stay, cost of hospitalization, etc.), will also demonstrate the significance of perioperative TEAS stimulation on postoperative GI function recovery of patients undergoing abdominal surgery. This study will provide further evidence as to whether TEAS should be included in enhanced recovery after surgery (ERAS) protocols for patients undergoing GI surgery.

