**Fig. 1 Fig1:**
[figure not shown]
Consolidated Standards of Reporting Trials (CONSORT) diagram for this trial

The study will continue for 24 months, and all the selected individuals will be stratified by type of surgery (i.e. gastric or colorectal procedure) and randomized into two groups: the TEAS treatment group (Group T) and the sham group (Group S). The researchers will conduct screening in accordance with the established criteria and pre-standard treatment plan. Data collection will start from the collection of basic data until the end of follow-up (Table 1).

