### Sample size calculation

Due to a lack of related reports on the preventive usage of TEAS in patients undergoing GI surgery, we evaluated the effectiveness of TEAS according to our pre-experimental results. A priority-effectiveness test was used and the ratio between the groups was 1:1. According to the pre-experimental results, a difference in time to first bowel sounds of 12 h was thought to be clinically significant and selected as the effect size. This result in a hazard ration of 1.5. The COX regression sample size calculation formula was used to complete the sample size estimation. We set unilateral α = 0.05 and power = 0.90; PASS 2011 software was used for sample estimation and a total of 256 effective cases were estimated. According to the above sample estimation result and assuming 10% patient loss, a minimum of 280 cases is required. Therefore, we have set the required number of cases in this study to 280 cases, including 140 cases in the TEAS group and 140 cases in the sham TEAS group. Our General Surgery Department performs 400–500 cases of GI surgery per year; consequently, this study period is set at 2 years.

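### Gastrin is compared across gastric and colorectal resections by tests with no surgery-type or baseline term, which costs power and makes the pre-to-post change in gastric patients hard to interpret

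*Protocol article*

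**What the plan says.** Outcome assessment makes plasma peptides a secondary endpoint and names gastrin as one of five examples: "To observe changes in plasma brain–gut peptides, such as 5-HT, SP, VIP, gastrin, and CCK, we will collect venous blood from patients before the operation". The full sampling schedule is "before the operation and on the first and third days after the operation". No analyte is restricted to one kind of operation.

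Study participants and recruitment covers both kinds: "We will recruit 280 patients scheduled to undergo laparoscopic resection of gastric and colorectal tumors". The abstract and Trial design (text below Fig. 1) make surgery type a stratification factor: "all the selected individuals will be stratified by type of surgery (i.e. gastric or colorectal procedure) and randomized into two groups".

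Statistical methods offers a t-test or rank sum test for continuous data. The relevant sentence reads "The t-test will be used for the normality and homogeneity of data". Neither surgery type nor the preoperative value appears as a model term, and gastrin is not mentioned there.

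The Introduction says what the peptide data are for: "Changes in the perioperative brain–gut peptides may prove that the regulation of GI function by TEAS stimulation plays a role through the brain–intestinal axis". That sentence concerns the peptides collectively and does not name gastrin.

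**The concern.** Gastrin differs from the other listed peptides because one of the two eligible operations acts on an organ that secretes it. If a gastric resection takes out gastrin-secreting tissue, it does so between the baseline and day 1 samples. The pre-to-post change in those patients is then partly or mostly a record of what was removed, whichever arm they are in. This physiology is general knowledge. The document does not state it, so it is an assumption here.

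Two consequences follow if the named tests are applied to all patients as written.

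- The gap between gastric and colorectal patients enters the error term of an unadjusted test, although the design already stratifies on that factor.
- A before-and-after gastrin change, shown alongside the other peptides, could be taken as a response of the brain–gut axis when it reflects the operation.

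If gastric patients also respond less to stimulation, the all-patient effect is diluted as well.

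**Working it through.** The document gives no figure for gastrin: no SD, target effect, power, gastric share or resection type. There is nothing of the plan's own to reproduce. What follows is an illustration on stated assumptions.

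**Inputs from the document.** 256 evaluable patients at 1:1, so n = 128 per arm. This figure was derived for the primary outcome and is borrowed here only as a patient count. The test is one-sided at 5%, from "We set unilateral α = 0.05 and power = 0.90", so the critical value is 1.645.

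**Assumed inputs.** Gastric share g = 0.2, 0.4 or 0.5. Within-stratum SD = 1. Difference between the strata in mean gastrin change D = 1 or 2 SD. TEAS effect d in colorectal patients set so that power is 80% if everyone responds and the strata do not differ:

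d = (1.645 + 0.842) × √(2/128) = 2.487 × 0.125 = 0.311 SD.

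**Formulas.**

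- Unadjusted SD = √(1 + g(1−g)D²). Stratum-adjusted SD = 1.
- All-patient effect = d if both strata respond equally, or (1−g)d if gastric patients do not respond.
- Power = Φ(effect / (SD × 0.125) − 1.645).
- Colorectal patients alone: Φ(d√(1−g) / 0.125 − 1.645).

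Example with g = 0.4, D = 2: SD = √(1 + 0.24 × 4) = 1.40. With equal response, Φ(0.311/0.175 − 1.645) = Φ(0.13) = 55.2%. With no gastric response the effect is 0.6 × 0.311 = 0.186, and Φ(0.186/0.175 − 1.645) = Φ(−0.58) = 28.1%.

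| g | D | Unadjusted, equal response | Adjusted, equal response | Unadjusted, no gastric response | Adjusted, no gastric response | Colorectal alone |
|---|---|---|---|---|---|---|
| 0.2 | 1 | 74.7% | 80.0% | 58.0% | 63.5% | 71.9% |
| 0.2 | 2 | 61.7% | 80.0% | 46.4% | 63.5% | 71.9% |
| 0.4 | 1 | 72.2% | 80.0% | 38.0% | 43.9% | 61.1% |
| 0.4 | 2 | 55.2% | 80.0% | 28.1% | 43.9% | 61.1% |
| 0.5 | 1 | 71.9% | 80.0% | 29.7% | 34.4% | 54.5% |
| 0.5 | 2 | 54.5% | 80.0% | 22.2% | 34.4% | 54.5% |

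The unadjusted columns treat the stratum mix as free to vary between arms. Stratified randomisation holds it nearly fixed, so the unadjusted test is in fact conservative. Its power is then Φ(effect/0.125 − 1.645 × SD). At g = 0.4, D = 2 with equal response this is Φ(2.487 − 2.303) = 57.3% instead of 55.2%, and with no gastric response Φ(1.492 − 2.303) = 20.9% instead of 28.1%. The true one-sided error rate there is Φ(−2.303) = 1.1% instead of 5%. The conclusion does not change.

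**Should gastric patients be left out of the test?** Let gastric patients keep a fraction f of the effect. The adjusted all-patient test is at least as powerful as colorectal alone when (1−g) + gf ≥ √(1−g), that is f ≥ [√(1−g) − (1−g)]/g. This gives 47% at g = 0.2, 44% at g = 0.4 and 41% at g = 0.5. Below those fractions the colorectal-only test is better; above them it throws information away.

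The gain from adjusting for the preoperative value is not computed, because no correlation between baseline and later values is given.

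**The case against.** The strongest reply is that the document never says the strata are pooled for gastrin. Statistical methods names broad families of tests and says an analysis plan will be developed. How one secondary biomarker is modelled is ordinary content for that plan, which is not at hand. This stands in part: pooling is an inference from the tests named. What remains is that those tests have no place for the stratification factor or the baseline already collected.

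Gastrin appears only once, in a list of examples, and the mechanism sentence in the Introduction does not name it. That also stands. A reader might infer that a null gastrin result will be held against the brain–gut pathway, but no text says so.

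A reader might also infer that the operation biases the TEAS comparison. It does not. Randomisation spreads the operative effect over both arms, and stratification keeps the mix of operations balanced. The cost is sensitivity, not validity.

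Finally, it is tempting to say that gastric patients cannot respond and that the test should use colorectal patients only. The document does not say which part of the stomach is removed or how many patients are gastric, so a zero response is the extreme case and not a fact. By the break-even above, dropping them loses power once they keep about 41–47% of the effect.

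**Conclusion.** The point holds as a minor improvement. Followed as written, the named tests give a noisier gastrin comparison than the design allows, and a pre-to-post change in gastric patients that may largely reflect surgery.

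The size is unknown. With strata 1 to 2 SD apart and 20–50% of patients gastric, omitting the stratum takes power from 80% to between 75% and 55% even if both strata respond equally. Further loss from dilution arises only if gastric patients respond less. These figures rest on assumed shares, shifts and effects, and on physiology from outside the document.

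It concerns one of five named peptides within a secondary outcome. The primary outcome and the sample size are untouched.

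**What to change.** State in the analysis text that postoperative gastrin is compared between arms in a model adjusted for the preoperative value and for surgery stratum. Include a treatment-by-stratum term and present the treatment effect separately for colorectal and gastric patients. Add that the within-patient gastrin change in gastric patients will not be treated as evidence about the brain–gut axis. Keep gastric patients in the inferential analysis.

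The cost is two or three sentences. The preoperative sample and the surgery type are already collected, and no patients or samples are added. Recruitment was still under way when the article was written (106 of 280), so this could be fixed ahead of the final analysis. The small downside is that stratum-specific estimates are less precise than the overall one, and the interaction term will have limited power.
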